#### Recruitment {15}

Participants will be recruited via advertisement flyers posted in the communities of Gunnison County, social media, word of mouth, employee email lists of WCU and GVH, local newspaper and magazine ads, churches, and through physician referral among the Gunnison County health care providers. To account for the logistical capacity of data collection, participants will be recruited in cohorts of 12 (randomized into intervention groups) where each cohort will complete the entire study before the next cohort begins. This will continue until 20 participants per intervention group have completed data collection.

### Assignment of interventions: allocation

#### Sequence generation {16a}

After completion of baseline testing and adaptive period, participants will be randomly allocated to a HIFT dose group at a 1:1:1 ratio by computer-generated random numbers. This will be conducted by [name], one of the investigators uninvolved with participant recruitment, enrollment, assessments, and exercise training. Randomization will be blocked in cohorts and stratified by sex. The block size will be concealed by this investigator until the primary endpoints have been analyzed.

#### Concealment mechanism {16b}

Throughout the study, randomization will be conducted by [name], utilizing a computer-generated sequence. All allocation sequences will be stored on their personal computer, and sequences will be concealed until the primary endpoints have been analyzed. Treatment allocation will not be released to the participants until after they complete baseline testing and the adaptive period. This investigator will not be involved in recruitment, enrollment, assessments, or any execution of the intervention. Thus, randomization will be conducted without any influence of the principal investigator and research assistants involved directly with recruitment, enrollment, and assessments of participants, as well as delivery of the intervention.

#### Implementation {16c}

[name] will communicate the treatment allocation to each participant via a personal email. This communication will only occur after the participant has been enrolled, completed baseline testing, and completed the adaptive period. Thus, allocation communication will be conducted without any influence on recruitment and enrollment.

## Assignment of interventions: blinding

### Who will be blinded {17a}

All data collection sheets and data analysis will be coded by the investigator assigning the interventions in order to blind the primary investigator and research assistants from intervention allocations. Data analysis, data collection, and exercise training will be conducted by the primary investigator and research assistants but not the investigator conducting the allocations. Due to the nature of the intervention, participants will not be blinded to their allocation but are strongly encouraged not to disclose their allocation or the allocation of other participants.

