#### Intervention description {11a}

For 3 weeks prior to the 12 weeks of training, participants will undergo exercise familiarization 2 days/week. Participants will then be randomized into 1 of 3 exercise dose groups (HIFT1, 1 session per week; HIFT2, 2 sessions per week; HIFT3, 3 sessions per week). Then, 12 weeks of supervised training will commence consisting of three 4-week phases, where intensity, duration of exercise, and recovery time are progressed each phase.

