##### Twelve-week HIFT training period

Participants will perform their allocated HIFT sessions. All sessions will use asynchronous music playing and be supervised by a Certified Medical Exercise Specialist (CMES) or specifically trained exercise science undergraduate and graduate students when the CMES is unable to attend. These personnel will facilitate exercise instruction, duration and effort monitoring, and data collection and provide standardized encouragement to participants. HIFT sessions will be scheduled on Monday, Wednesday, and Friday in the morning and during the lunch hour, where participants can attend according to their personal schedules and allocated dose group. HIFT session attendance will be organized to ensure between 2 and 5 people at each scheduled time. The training protocol will be divided into three 4-week phases where exercise is progressed in both intensity and volume during each phase, with the last week of each phase being digressed to 60–70% of the volume [80, 81].

Progression of volume will follow the characteristics in Table 1. Progression of load will be individualized for each exercise using the session RPE (sRPE) method, with a target sRPE ≥ 7 (Borg CR10) after each set within the workout [76–79]. The aerobic intensity target (HR ± 5 beats of VT2) will remain throughout. To quantify these intensity targets, HR and sRPE will be measured immediately after each set and recorded by exercise personnel. If a participant’s sRPE falls below 7 or HR falls below the established target, the load will be incrementally increased upon the next training session. Examples of load progression are adding weight or modifying the position of the body to increase resistance or adding elements of velocity to the movement. This personalized method ensures that load/effort is progressed based on each individual’s rate of development and is easily translated into a real-life training session. It also affords the flexibility to be applied to a wide range of exercises and precludes the need for specific maximal strength assessment such as 1RM for subsequent prescription of load percentages.

**Table 1 Tab1:** Progression characteristics of the 12-week training period

Training parameters	Phase 1		Phase 2		Phase 3	
	Weeks 1–3	Week 4	Weeks 5–7	Week 8	Weeks 9–11	Week 12
Total conditioning duration (min)	36	24	38	26	38	26
Net exercise time (min)	24	16	26	18	28	20
Net recovery time (min)	12	8	12	8	10	6

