### Data management {19}

To keep participant personal health data private, all paper data with personal health information, including consent forms and health history documents, will be stored in a secured, locked file cabinet in the principal investigator’s office on WCU’s campus. Only the principal investigator and listed protocol contributors will have access to this personal data.

Participants’ names will be coded to protect identity on all assessments, testing data, and exercise logs. All coded paper data will be stored in a locked file cabinet in the WCU HAP Lab office. These data will be entered electronically at the participating site where the data originated from by the principal investigator. Two trained research data entry personnel will separately verify the electronic copy for validity and range checks. Any errors will be reported to the principal investigator and protocol contributors, and corrections will be made. These electronic data will be stored in a secure (password-protected) database in duplicate, on both WCU’s and AUT’s campus networks to prevent unauthorized access. Incremental back-ups will be performed on a daily basis to prevent data loss.

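### Coding the data sheets cannot blind the principal investigator and research assistants, because the protocol has the same people deliver the training that defines the arms

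*Protocol article*

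**What the plan says.** Section Who will be blinded {17a} names the means: "All data collection sheets and data analysis will be coded by the investigator assigning the interventions". It gives the purpose as "in order to blind the primary investigator and research assistants from intervention allocations". The sentence that follows assigns the work: "Data analysis, data collection, and exercise training will be conducted by the primary investigator and research assistants", with only the allocating investigator left out. Participants are openly unblinded and are asked not to reveal their own or others' allocation.

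Section Concealment mechanism {16b} joins the same roles again. It describes the principal investigator and "research assistants involved directly with recruitment, enrollment, and assessments of participants, as well as delivery of the intervention".

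The next section, Procedure for unblinding if needed {17b}, reserves unblinding for the exceptional case of an adverse effect, which presumes a blind to break.

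**The concern.** Allocation in this trial is a visible schedule. A code on a sheet can hide a tablet or a laboratory sample. It cannot hide from a trainer how often a participant comes to train.

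If the people who train also measure and analyse, two risks follow. The first is detection bias in measurements that depend on the operator or on the participant's effort. The second is analysis decisions made with the arms known. A results paper that followed {17a} would also claim a safeguard for these staff that the design does not provide.

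**Working it through.** There is no stated figure to reproduce. The check sets the sections side by side and adds one count.

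**1. What separates the arms.** Intervention description {11a}: "HIFT1, 1 session per week; HIFT2, 2 sessions per week; HIFT3, 3 sessions per week". Session content within a week is standardized across groups, so weekly frequency is the only difference.

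**2. Who sees it.** In Twelve-week HIFT training period, "participants can attend according to their personal schedules and allocated dose group". Attendance is arranged to put 2 to 5 people in each slot, and exercise personnel record heart rate and perceived effort after every set. Section {11c} keeps the small groups the same for all 12 weeks, and section Sample size {14} sets cohorts of 12. Staff who organize or supervise these sessions learn each participant's weekly frequency in the ordinary course of the work.

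**3. Whether the code hides it.** Data management {19} places participant codes on assessments, test data and exercise logs alike, and then says: "These data will be entered electronically at the participating site where the data originated from by the principal investigator". The person entering the data can therefore read the dose from the log.

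**4. Session count.** Assume that the 80% adherence rule in Statistical methods {20a} is counted in sessions.

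| Arm | Full attendance | 80% of full | Adherent range |
|---|---|---|---|
| HIFT1 | 12 × 1 = 12 | 9.6, so at least 10 | 10–12 |
| HIFT2 | 12 × 2 = 24 | 19.2, so at least 20 | 20–24 |
| HIFT3 | 12 × 3 = 36 | 28.8, so at least 29 | 29–36 |

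The ranges do not overlap. A session total identifies the arm of every adherent participant, and applying the rule at all requires knowing the allocated dose.

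**5. Which outcomes are exposed.**
- *Largely protected:* blood draws and DEXA, done at the hospital by its own staff (Eligibility criteria {10}; {18a}), and the lipoprotein profile with ApoB, insulin and glucose, assayed at an outside laboratory ({18a}).
- *Exposed:* forearm plethysmography, a primary outcome measured at the university laboratory, whose measurements {10} gives to exercise scientists.
- *Partly exposed:* VO2max from a treadmill test to volitional exhaustion at the same laboratory.
- *Exposed in the analysis:* {20a} and {20c} exclude participants for a noticeable change in eating or activity, and {20c} leaves it to be judged whether intention-to-treat is appropriate and whether to impute.

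**The case against.** The strongest reply is that the outcomes that matter most are out of reach. ApoB, on which the sample size rests, and most of the primary aim come from hospital staff or an outside laboratory, and the trial calls itself exploratory. This stands, and it limits the point. A reader might infer that no assessment is protected from knowledge of the arm, but the document does not support that: those staff do not deliver training. Equally, no section says that they are blinded.

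Second, there are safeguards. The treadmill test has a verification bout at 105% of maximal workload, a ±3% agreement criterion and a repeat if VO2max is not reached. Plethysmography uses set cuff pressures and timings. These limit operator and effort bias but do not remove it.

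Third, the analyst's freedom is bounded. Diet change is tied to a statistical difference, although the test is not named, and non-adherence triggers both intention-to-treat and per-protocol sets. This also stands in part; the choices listed in the working remain open.

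Fourth, the overlap is not shown person by person. Sessions are run by a certified specialist or trained students, and research assistants is a collective term. It is possible that some assistants would never test a participant they trained. But no section separates the roles, and {16b} and {17a} both join them.

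A reader might also count ventilatory thresholds among the outcomes at risk. The document does not support this. The graded exercise test outcomes are maximal heart rate, VO2 and workload, and the second threshold serves to set a training heart-rate target already in use before randomization.

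**Conclusion.** The point holds for the people whom {17a} names. The section claims a blind for the principal investigator and research assistants and then gives them the tasks that reveal the arm. The unblinding procedure in {17b} inherits the error.

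The consequence is confined to forearm plethysmography, in part VO2max, and analyst choices. Its size cannot be calculated from the document, and the powered outcome, ApoB, is largely protected. It should be corrected, but it does not undermine the ApoB measurement.

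The conclusion rests on three assumptions: that primary and principal investigator are one role, since both terms are used for the person taking consent; that the 80% rule counts sessions; and that research assistants are not divided by task in an arrangement the article leaves out. If such a division exists, {16b} and {17a} misdescribe it and still need correcting.

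**What to change.** **Wording.** State in {17a} that participants, trainers and the principal investigator are not blinded, and reconcile {17b} with that. Claim no blinding that is not actually arranged, including for hospital and laboratory staff.

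**Assessment.** Within the existing team, where rostering allows, have assistants who did not train a given cohort run its post-test plethysmography and treadmill test, with scripted encouragement. Have plethysmography traces read from files coded without arm or attendance. If staffing does not allow this, report these assessments as unblinded; the document gives no staff numbers, so feasibility cannot be judged here.

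**Analysis.** Have an advising investigator with no access to session logs or the allocation sequence run the primary analysis on arm-coded data. The allocating investigator may look like a natural independent analyst but is not one: that person generates and stores the sequence, emails each allocation, and is excluded from analysis by {17a}.

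**Cost.** Some rostering effort, a few changed sentences, and a paper that reports a largely open trial.

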### Procedure for unblinding if needed {17b}

To maintain the quality and legitimacy of the clinical trial, unblinding should only occur in the exceptional circumstance that a participant had an adverse effect from the intervention. In this case, knowledge of the intervention allocation is absolutely essential for further management of the participant’s safety.

## Data collection and management

### Plans for assessment and collection of outcomes {18a}

#### Primary outcomes

##### Blood analysis

Participants will visit GVH for fasted blood draws performed by a trained phlebotomist at baseline and 48–72 h after the exercise intervention. Venipuncture of the anti-cubital vein will be performed, and blood will be collected into heparinized tubes. Five milliliters of blood will be drawn for the lipoprotein metabolism profile (LMPP), 1 mL will be drawn for insulin, 1 mL will be drawn for glucose, 1 mL will be drawn for HbA1c, and 1 mL will be drawn for hematocrit. All blood collected for the LMPP, insulin, and glucose will be frozen at − 80 °C and sent to Mayo Clinic Laboratories in Denver, CO. All results will be communicated back to GVH. The LMPP consists of an ApoB count, Lp[a] count, and cholesterol and triglyceride content of each lipoprotein subclass (VLDL, LDL, HDL). Hematocrit is calculated to adjust for plasma volume changes applied to the cholesterol and triglyceride content measures. Glucose and insulin measures will be used to calculate insulin resistance (IR) using the homeostatic model assessment (HOMA) [83, 84].

##### Endothelial function

Endothelial function will be assessed at baseline and 48–72 h after the last exercise bout of the intervention. Fasted, endothelial-dependent vasodilation of the non-dominant arm will be measured using venous occlusion strain gauge plethysmography (EC6 Strain Gauge Plethysmography System & Rapid Cuff Inflation System, Hokanson Inc., Bellevue, WA). To begin, forearm volume will be measured by the water displacement method. Then, the arm will be elevated to the level of their heart, a pneumatic cuff will be placed around the wrist and upper arm, and a strain gauge will be fixed around their lower arm. Once all measuring devices are attached and ready, the contralateral arm will be used to measure HR and BP until stable resting values are obtained (after 15 min of supine quiet rest). Next, basal blood flow will be measured for 5 min. The wrist cuff will be inflated to 220 mmHg, and the upper arm cuff will cycle between 50 and 0 mmHg every 8 and 7 s for the entire 5 min. Then, the brachial artery will be occluded for 5 min at a pressure of 220 mmHg. At the 4-min mark of the occlusion period, the wrist cuff will be inflated to 220 mmHg again. At the end of the occlusion period, the upper arm cuff will be deflated to assess reactive hyperemia for 5 min. Peak forearm blood flow and 60-s hyperemia blood flow will be quantified.

#### Secondary outcomes

##### Body composition

Participants will visit GVH to be measured for body composition via dual X-ray absorptiometry (DEXA) at baseline and 48–72 h after exercise intervention.

##### Self-perceived fitness

To assess the participants’ self-perceived overall fitness, the International Fitness Scale (IFIS) will be administered at baseline and after the exercise intervention [85, 86]. This scale contains five questions with a Likert-type answering option (very poor, poor, average, good, and very good) associated to the elements of physical fitness: cardiorespiratory endurance, muscular strength, speed-agility, and flexibility.

##### Graded exercise test

Baseline and post-training cardiorespiratory fitness will be measured via a graded exercise test (GXT) on a power treadmill (CT850, Spirit Fitness, Jonesboro, AR) in the HAP Lab. Participants will be instructed on the rate of perceived exertion scale (RPE) and walking protocol, outfitted with a HR monitor (Polar F1, Polar USA, Warminster, PA), connected to a metabolic cart (Oxycon Mobile, CareFusion Respiratory Care, Yorba Linda, CA) and positioned on the treadmill. The GXT will begin with a 5-min warm-up at a self-selected pace, gradually reaching the pace they will maintain throughout the test. A modified Balke and Ware protocol will be used where participants will maintain their constant speed and incline will be increased by 1% each minute until volitional exhaustion [87]. Breath-by-breath gas exchange and continuous HR data will be collected and averaged every 15 s. RPE will be measured in the last 10 s of each minute. Participants will continue until volitional exhaustion. The first and second ventilatory thresholds (VT) will be identified and calculated as the point in which the plotted ventilation rate makes an a-linear increase. Maximal HR, VO_2_, and workload will be recorded. Participants will rest passively for 20 min after the completion of the GXT, then perform a verification trial to confirm VO_2max_ [88–90]. For the verification trial, participants will walk on the treadmill at a workload of 105% of their maximal workload during the GXT (last fully completed stage) until volitional exhaustion. If the VO_2max_ of the verification bout and GXT are within ± 3%, true VO_2max_ will be considered achieved [88, 90]. If participants are unable to reach VO_2max_, they will be asked to repeat the trial after a 24-h rest.

#### Tertiary outcomes

##### Exercise questionnaires

To assess the participant’s level of “enjoyment” and “intention to continue” their allocated HIFT intervention, a questionnaire will be administered 48–72 h after the exercise intervention. For enjoyment assessment, the Physical Activity Enjoyment Scale (PACES) will be used [91]. The PACES is an 18-item, 7-point, bipolar rating scale. For the intention to continue assessment, two additional items will be added regarding (1) how likely the participant would continue performing that modality (0 = very unlikely, 10 = very likely) and (2) how many days per week the participant would consider performing that modality (0–7 days) [92, 93].

### Plans to promote participant retention and complete follow-up {18b}

Exercise supervision and encouragement will take place during every session of the intervention to promote participant retention and safety. Participants will be given a copy of all HIFT workouts and personal health data at the end of the trial which may serve as an incentive to continue the habit of regular exercise on their own.

### Data management {19}

To keep participant personal health data private, all paper data with personal health information, including consent forms and health history documents, will be stored in a secured, locked file cabinet in the principal investigator’s office on WCU’s campus. Only the principal investigator and listed protocol contributors will have access to this personal data.

Participants’ names will be coded to protect identity on all assessments, testing data, and exercise logs. All coded paper data will be stored in a locked file cabinet in the WCU HAP Lab office. These data will be entered electronically at the participating site where the data originated from by the principal investigator. Two trained research data entry personnel will separately verify the electronic copy for validity and range checks. Any errors will be reported to the principal investigator and protocol contributors, and corrections will be made. These electronic data will be stored in a secure (password-protected) database in duplicate, on both WCU’s and AUT’s campus networks to prevent unauthorized access. Incremental back-ups will be performed on a daily basis to prevent data loss.

### Confidentiality {27}

Any potential and enrolled participant information will be kept confidential, only identifiable by primary investigators. Codes will be used instead of names on all documents. For all data collected at WCU and GVH, the standard HIPAA regulations and procedures will be followed. Each participant’s information will be combined with other people taking part in the study when results are shared or presented in materials.

### Plans for collection, laboratory evaluation, and storage of biological specimens for genetic or molecular analysis in this trial/future use {33}

All biological specimens will be destroyed after data is recorded. No specimens will be retained for future use.

## Statistical methods

### Statistical methods for primary and secondary outcomes {20a}

Only data from participants who complete ≥ 80% of total exercise intervention and with no noticeable change in eating (statistically different energy consumption and macronutrient distribution) and physical activity habits will be included [97, 99, 100]. All data will be analyzed using the Statistical Package for the Social Sciences (IBM SPSS v25, Armond, NY). Descriptive data if normal will be presented as mean ± SD, or median and interquartile range if not normal; the significance level of all comparative data will be set as *p* ≤ .05, and normality will be assessed using a Kolmogorov-Smirnov test. If normality exists, parametric tests will be used, if normality does not exist, non-parametric tests will be used. Effect sizes (ES) and confidence intervals (CI) will be calculated on the results of all dependent variables. Paired *t*-tests will be used to evaluate the significant differences between pre- and post-measures of both primary and secondary physiological outcomes within each group. A one-way ANOVA will be used to compare the primary and secondary outcomes pre-post mean change between the three groups. When indicated by a significant *F* value, post hoc analysis will be determined using the Bonferroni adjustment for multiple comparisons. The median, mode, and interquartile ranges of the IFIS and PACES data will be calculated for each of the three groups. Should missing data in outcomes occur, a linear-mixed model will be conducted instead of ANOVA as this test accounts for missing data.

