### Methods in analysis to handle protocol non-adherence and any statistical methods to handle missing data {20c}

Participant adherence will be determined by completion of ≥ 80% of total exercise intervention and no noticeable change in eating and physical activity habits, assessed by the Block questionnaires. Should non-adherence occur, outcome variables will be tested using two analysis sets: the intention-to-treat set, considering all randomized participant data regardless of intervention adherence, and the per-protocol set, considering only data from participants who complete ≥ 80% of the total exercise intervention. Analyses will be performed to examine the effect of the different strategies on the conclusions. If intention-to-treat analyses are determined appropriate, reasons for withdrawal will be reported and compared qualitatively. If missing outcome variables occur, imputation of missing data will be considered. To account for missing data, a linear mixed-model analysis will be used to determine if there are differences in the primary outcome variable of ApoB.

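### The main statistical section analyses only participants found adherent after randomisation, the non-adherence section tests all randomised participants as well, and neither set is named primary

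*Protocol article*

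**What the plan says.** Three parts of the Protocol article bear on this point.

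- **Statistical methods for primary and secondary outcomes {20a}.** The first sentence sets the analysed data: "Only data from participants who complete ≥ 80% of total exercise intervention and with no noticeable change in eating" "and physical activity habits will be included". The paired t-tests and the three-group ANOVA on change that follow are described for those data. The sentence has no qualifier and refers to no other analysis set.
- **Methods in analysis to handle protocol non-adherence {20c}.** Adherence is defined by the same three elements: attendance, eating and activity. The section then says "Should non-adherence occur, outcome variables will be tested using two analysis sets: the intention-to-treat set", with ITT described as "considering all randomized participant data regardless of intervention adherence". The second set is per-protocol, defined only by completing at least 80% of the intervention. The effect of the different strategies on the conclusions is to be examined. A later sentence reads "If intention-to-treat analyses are determined appropriate, reasons for withdrawal will be reported and compared qualitatively". Neither set is called primary.
- **Intervention description and Three-week adaptive period.** Randomisation comes before the 12 weeks of training, and the arms are allocated 1, 2 or 3 sessions per week.

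**The concern.** Randomisation makes the three dose groups comparable at the start of training. A filter on what participants do afterwards can undo this, because those who pass it in one arm need not resemble those who pass it in another. Here the filter depends on the allocation itself: 80% is a share of the assigned sessions, so the task differs by arm. Diet and outside activity could also respond to dose. The protocol gives its own reason to expect adherence to vary with dose, since its hypotheses include lower enjoyment and lower intention to continue at higher doses.

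If {20a} is followed as written, the ANOVA does not compare the arms as randomised. If {20c} is followed, two results exist for each outcome and nothing says which one carries the conclusion. This affects every primary and secondary outcome, including the ApoB comparison of HIFT3 with HIFT1, for which the sample size section claims that superiority will be established.

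**Working it through.** **1. The two sections side by side**

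| Participant | {20a} | {20c}, ITT set | {20c}, per-protocol set |
|---|---|---|---|
| ≥ 80% attendance, diet and activity unchanged | included | included | included |
| ≥ 80% attendance, diet or activity changed | excluded | included | included |
| < 80% attendance | excluded | included | excluded |

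The second row shows that the adherent set of {20a} and the per-protocol set of {20c} are different sets. That participant is non-adherent under the definition that opens {20c}, yet belongs to its per-protocol set.

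**2. What the 80% rule asks of each arm**

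Allocated sessions are 1, 2 or 3 per week × 12 weeks. The requirement is 0.8 × N, rounded up.

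- HIFT1: 0.8 × 12 = 9.6, so 10 of 12 (may miss 2)
- HIFT2: 0.8 × 24 = 19.2, so 20 of 24 (may miss 4)
- HIFT3: 0.8 × 36 = 28.8, so 29 of 36 (may miss 7)

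**3. Retention under two assumed attendance patterns**

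The protocol gives no adherence rates, so both patterns are assumptions.

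*(a) Fixed sessions.* Sessions are independent with the same attendance probability p in every arm. Retention is P(Binomial(N, p) ≥ required sessions).

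| p | HIFT1 | HIFT2 | HIFT3 |
|---|---|---|---|
| 0.75 | 39% | 25% | 29% |
| 0.80 | 56% | 46% | 57% |
| 0.85 | 74% | 71% | 84% |
| 0.90 | 89% | 92% | 98% |

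*(b) Movable sessions.* Each of the three offered days is available with probability p and a session can move to another day. Weekly attendance is min(quota, Binomial(3, p)), simulated over 12 weeks.

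| p | HIFT1 | HIFT2 | HIFT3 |
|---|---|---|---|
| 0.80 | 100% | 99% | 57% |
| 0.85 | 100% | 99.8% | 84% |
| 0.90 | 100% | 100% | 98% |

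Retention differs by arm under both patterns, but the order does not agree. At p = 0.85, HIFT3 keeps more than HIFT1 under (a) and fewer under (b).

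**4. Illustrative size of the bias, with no true effect**

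Assumptions: the correlation between adherence and ApoB improvement is ρ = 0.3. The SD of change is 25 mg/dL, borrowed from the baseline SD in the sample size section because no SD of change is stated. HIFT1 keeps everyone. HIFT3 keeps a share f from the upper end of adherence.

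Bias = ρ × SD × φ(z) / f, where z cuts off the lower 1 − f of a standard normal.

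- f = 0.84: 0.3 × 25 × 0.243 / 0.84 = 2.2 mg/dL
- f = 0.57: 0.3 × 25 × 0.393 / 0.57 = 5.2 mg/dL

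For scale, 15% of the baseline mean of 129 is 19.35 mg/dL, so these are 11% and 27% of the planned reduction.

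**5. Effect on the planned test**

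One-way ANOVA with 20 per arm, SD 25 and a bias b in HIFT3 only. The noncentrality is λ = 20 × (2/3) × b² / 625.

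- b = 2.2: λ = 0.10, omnibus rejection 5.7%
- b = 5.2: λ = 0.58, omnibus rejection 9.4%

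The nominal rate is 5%. With the planned Bonferroni step after a significant F, the rate of a false HIFT3-versus-HIFT1 finding goes from 1.6% to about 2% and 4%.

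**The case against.** **ITT is planned.** This largely stands. Anyone excluded under {20a} is non-adherent under {20c}, which triggers the ITT set. If nobody is non-adherent, the two sets coincide. A reader might infer from "If intention-to-treat analyses are determined appropriate" that running ITT is itself optional. The sentence does not say so: grammatically, the clause governs only the reporting of withdrawal reasons. It is loose wording. What remains is that {20a} still excludes the data that {20c} includes, and no set has precedence.

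**The filter favours the higher dose.** A reader might infer this, on the view that only the most committed HIFT3 participants reach 29 sessions while nearly all of HIFT1 passes. That needs missed sessions to move freely between days. The protocol says sessions run on three days "where participants can attend according to their personal schedules and allocated dose group", but it also keeps the small groups the same throughout, organises attendance by slot and schedules participants for their sessions. Weekly swapping is not established, and with fixed sessions the retention order can reverse. The documents do not support a direction.

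**Exclusions will leave the trial short of power.** This too might be inferred from the 5% dropout allowance. But the sample size and recruitment sections continue recruitment until 20 per group have completed. Whether completing means passing the {20a} filter is not stated, so no power loss can be asserted.

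**The trial is exploratory and asks about dose, so analysing those who received the dose has a rationale.** It does, as a secondary view. The sample size section nevertheless aims at superiority of HIFT3 over HIFT1, and that claim needs one named analysis set that keeps the randomised groups.

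**Conclusion.** The point holds as a conflict in the text and a risk of bias. Section {20a} restricts all primary and secondary analyses to a subset selected after randomisation. Section {20c} adds an all-randomised set without ranking it, and uses a second definition of the adherent set. This follows from the wording alone and needs no assumption.

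The filter's threshold depends on the allocated dose, so it can keep different shares and kinds of participants by arm and may bias the dose comparison. The direction and size of any bias are unknown. The figures of about 2 to 5 mg/dL and an omnibus false-positive rate of about 6-9% rest on ρ = 0.3, an SD of change of 25 mg/dL, HIFT3 retention of 84% or 57%, and full retention in HIFT1. None of these is given by the protocol. At 90% availability, HIFT3 retention is 98% even with movable sessions, and the effect would be small. The case for change rests on the unranked and inconsistent sets, with the figures showing only that the consequence need not be trivial.

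**What to change.** 1. In {20a}, replace the first sentence with: *The primary analysis of all outcomes includes all randomised participants in their allocated arm, whatever their attendance, diet or activity.*
2. In {20c}, name ITT as the primary set without condition. Remove the clause that makes the two sets depend on non-adherence occurring and the clause about ITT being judged appropriate. Report reasons for withdrawal in any case.
3. Define one per-protocol set, in the same words in both sections. State whether it uses attendance alone or attendance with diet and activity. Always report it, labelled as a sensitivity analysis.

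The linear mixed model already planned in both sections can serve participants with missing outcomes.

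The cost is a change of wording. The ITT effect may be somewhat smaller than the effect among adherent participants, but the latter is still reported.
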